## 8.9 Missing data

Data will be classified in two ways, according to the degree of completion: missing responses (questionnaires with one or more missing responses) or missing questionnaire (questionnaires with more than half missing responses). These two cases will be managed differently in the analysis process, as described below:

### 1. *Missing responses*

The expected proportion is 2%, as reported in the EORTC QLQ-C30 Scoring Manual,[66] with missing values casually distributed in the two groups. To reduce the proportion of missing data, patients who have not filled in all fields at the end of completion will see a banner reminding them to do so, or to state unwillingness to respond. During data analysis, if a response is given for at least half of the items, the missing values are assumed to correspond to the mean of the given responses and the imputation method deemed most appropriate will be applied. If the number of missing data is greater than the half of the items, the questionnaire will not be considered valid.[66]

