### 8.1 INSTRUMENTS FOR OUTCOME MEASUREMENT

#### EORTC QLQ-C30

Quality of life, primary endpoint of the study, will be assessed with the validated Italian version of the European Organisation for Research and Treatment of Cancer Quality of Life Questionnaire-Core 30 items (EORTC QLQ-C30) [Apolone 1998], specific for patients with cancer. The tool is self-administered, and comprises 30 questions, 24 of which form nine multi-item scales representing the different aspects, or domains, of QoL: a global health status / QoL scale, five functional scales (physical, role, emotional, cognitive and social), and three symptom scales (fatigue, pain, nausea and vomiting), as well as 6 single items assessing additional symptoms (dyspnoea, loss of appetite, insomnia, constipation, diarrhea) and perceived financial impact of the disease).

As required in the Consort PRO extension [Calvert 2013], we briefly describe the ways the instrument and relative parameters for the assessment of the main endpoint were selected.

Various tools validated in many languages exist in the literature for the measurement of HRQoL, but two of them are most commonly used: the EORTC QLQ-C30 [Osoba 1994] and the FACT-G [Cella 1993] (Functional Assessment of Cancer Therapy-General). Luckett et al. [Luckett 2011] report an interesting comparison between the two tools, concerning content, scale, structure, psychometric properties, and other aspects, and constructed an algorithm which helps researchers in choosing the more adequate questionnaire according to the items of interest. Another recent work [King MT 2014] compares the two instruments' "responsiveness", or sensitivity to change, the most important property of a questionnaire used within a trial aiming to demonstrate the impact of an intervention, defined as the ability of an instrument to detect the minimal change considered to be clinically important by patients [Uwer 2011], and statistical efficiency, i.e. the sample size needed to detect such effects. Considering the nature of psychosocial interventions implemented in this study, which we hypothesize to mainly impact the social and emotional domains, and following the indications of the aforementioned papers, the QLQ-C30 was selected.

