## **8.2 Variable coding**

The following main patient demographic and clinical characteristics are collected at baseline to describe the study population and determine factors associated with quality of life:

- Date of birth (dd/mm/yyyy)
- Gender (M/F)
- Civil status (married or living with partner, other)
- Education (primary, high-school and above)
- Date of diagnosis (dd/mm/yyyy)
- Presence of metastases (yes/no)
- Cancer site
- ECOG performance status
- Type of treatment (IV chemotherapy , oral drugs, molecular target drugs)

At three-month follow-up, presence of disease progression will also be recorded (yes/no). For questionnaires where information was missing (less than half of items was completed), reasons for non-completion will also be noted, i.e. patient withdrawal, patient refusal to complete the item, worsening of patient's health conditions hindering completion, patient lost to follow-up or deceased (see paragraph 8).

As for coding of QLQ-C30 questionnaire variables, responses are given on likert scales and the sum of assigned values yields the score for each of the 15 domains. Highest values in the symptom domain (e.g. Diarrhea, weakness, vomiting etc.) will indicate severe symptomatology. Highest values in the other domains will indicate better quality of life. Scores of each domain are linearly transformed into a 0-100 scale, where 0 and 100 are assigned to the lowest and highest possible value, respectively.

For the HADS-D scale [Annunziata 2011] a cut-off of >7 will be used, a score considered clinically significant (i.e. patients scoring above this value may benefit from psychological support therapy) and with high sensitivity (0.86) and specificity (0.81) [Vodermaier 2011]. Missing values will be replaced with

the mean of the available values for anxiety or depression, if not more than four values are absent. The NEQ detects the presence of different types of needs using dichotomic choices (yes/no). It will enable to assess the frequency of needs and to compare it across the two detection periods (baseline and follow-up). Specifically, this information will allow to determine whether the HQIS is effective in reducing needs and whether this also corresponds to a positive effect on quality of life.

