## **REPORTING FORM**

### **Compilazione a cura dell'infermiere di ricerca**

**1. Se il paziente non ha compilato tutti e 3 i questionari o almeno uno dei questionari presenta meno del 50% degli item, indicare la motivazione:**

- ☐ Si rifiuta di completare il questionario [1]
- ☐ Le condizioni di salute non consentono di proseguire[2]
- ☐ Altro [3], specificare [3.1] \_\_\_\_\_

|                                                    |         |             |
|----------------------------------------------------|---------|-------------|
| VALUTAZIONE FOLLOW-UP – a 3 mesi dall'arruolamento | Centro  | Paziente n° |
|                                                    | □ □ □ □ | □ □ □ □     |

VALUTAZIONE DELLA QUALITÀ DELLA VITA CON EORTC QLQ-C30

VALUTAZIONE DELLA DEPRESSIONE E DELL'ANSIA CON HADS

VALUTAZIONE DEI BISOGNI PSICOSOCIALI CON NEQ

|                                                    |         |             |
|----------------------------------------------------|---------|-------------|
| VALUTAZIONE FOLLOW-UP – a 3 mesi dall'arruolamento | Centro  | Paziente n° |
|                                                    | □ □ □ □ | □ □ □ □     |

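### Section 8.9 words the half-of-items rule for the QLQ-C30 at questionnaire level, although the primary analysis is by domain

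*Protocol*

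**What the plan says.** Protocol section 8.9 divides incomplete data into two classes. One is a questionnaire with some missing responses. The other is a "missing questionnaire (questionnaires with more than half missing responses".

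For the first class, the subsection on missing responses says that "if a response is given for at least half of the items, the missing values are assumed to correspond to the mean" of the answers given, and in the same sentence that "the imputation method deemed most appropriate will be applied". For the other side of the threshold it says: "If the number of missing data is greater than the half of the items, the questionnaire will not be considered valid".

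The same threshold appears elsewhere, mainly as the trigger for recording reasons for non-completion. Section 8.2 has "For questionnaires where information was missing (less than half of items was completed", and the nurse's reporting form in Attachment IV asks for a reason when "almeno uno dei questionari presenta meno del 50% degli item" (at least one questionnaire has under 50% of its items).

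Three other statements bear on the rule:
- Section 8.1 says that the instrument "comprises 30 questions, 24 of which form nine multi-item scales" and that the EORTC manual will be followed for use, analysis and interpretation.
- Section 8.7 analyses the emotional and social domains one at a time as the primary outcome.
- Section 8.2 fills missing HADS items from the anxiety or the depression values, that is, by subscale. No corresponding scale-level sentence is given for the QLQ-C30.

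**The concern.** The primary outcome is two domain scores, while the rule that decides whether data are usable looks at all 30 items. The two can disagree in both directions. A complete primary domain can be thrown away because the rest of the form is empty. A primary domain with no answers can be treated as available because the rest of the form is full.

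In the second case the wording leaves open which answers supply the fill-in mean. If they come from other scales, the social or emotional score reflects physical function and symptoms. The mean would also mix items coded 1 to 4, where high is worse, with the two global items coded 1 to 7, where high is better. The social domain is the more exposed of the two, because it has only two items.

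The discard half also affects the analysis population. Section 8.8 requires assessments at baseline and at three months, so if an invalid questionnaire counts as no assessment, one such form removes the patient from the principal analysis.

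**Working it through.** The plan gives no figure for this rule, so there is none to reproduce. The check is a count of items, followed by a size estimate.

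**Inputs**
- 30 items (section 8.1), so half is 15.
- Items 1 to 28 are coded 1 to 4, and items 29 and 30 are coded 1 to 7 (form in Attachment IV).
- Emotional = items 21 to 24 and social = items 26 and 27. This is an assumption from the item wording on the form; the protocol does not list items by scale.
- Expected missing responses 2% (section 8.9), 720 patients and 20% drop-out (section 8.6).

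**Step 1. Answer patterns under section 8.9 and under a within-scale rule** (at least 2 of 4 emotional items, at least 1 of 2 social items)

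| Items answered | Count | Section 8.9, literally | Emotional answered | Social answered | Within-scale rule |
|---|---|---|---|---|---|
| 17 to 30 only | 14/30 = 47% | not valid | 4/4 | 2/2 | both scored |
| all but 26 and 27 | 28/30 = 93% | valid | 4/4 | 0/2 | emotional scored, social missing |
| 1 to 16 only | 16/30 = 53% | valid | 0/4 | 0/2 | both missing |
| all but the six primary items | 24/30 = 80% | valid | 0/4 | 0/2 | both missing |

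The first row discards complete primary data. The other three accept a questionnaire in which a primary domain is empty.

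**Step 2. What a pooled mean would produce, if it were used.** Mapping items coded 1 to 4 linearly to 0–100, with high as better, gives score = {1 − (mean − 1)/3} × 100. Suppose both social items are skipped, the other 26 items coded 1 to 4 are all 1, and both global items are 7:
- mean = (26 × 1 + 2 × 7)/28 = 40/28 = 1.43
- score = {1 − 0.43/3} × 100 = 85.7
- from the 26 items alone the score would be 100, a gap of 14.3 points caused only by the global items' different coding.

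**Step 3. How often.** Assessments: 720 at baseline plus 720 × 0.8 = 576 at follow-up = 1,296. If 2% is a per-item rate and omissions are independent:
- both social items missing: 0.02² = 0.0004, and 1,296 × 0.0004 = 0.52 assessments (576 × 0.0004 = 0.23 at follow-up)
- all four emotional items missing: 0.02⁴ = 1.6 × 10⁻⁷
- more than 15 of 30 missing: about 7 × 10⁻²⁰.

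If 2% instead means questionnaires with any missing response, 0.02 × 1,296 = 26 assessments are incomplete in any way. That is a ceiling for those lacking both social items, not an estimate.

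**Step 4. Effect on a mean.** If a fraction f of assessments in one condition only carried an error of 14.3 points, that condition's mean would move by 14.3f: 0.006 points at f = 0.04%, 0.14 at an assumed 1%, and 0.7 at an assumed 5%. Reaching the lower end of the 3 to 8 point target difference in section 8.6 would need f = 3/14.3 = 21%.

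**The case against.** The strongest reply is that section 8.9 is a loose summary of an outside procedure. Section 8.1 says the EORTC manual will be followed, section 8.9 cites the scoring manual for this rule, and section 8 leaves measure calculation and missing data to the SAP. The fill-in sentence refers to items without saying all 30, section 8.2 scores each domain separately, and the added imputation clause means the mean is not clearly the final method. On this view, averaging across scales is the least sensible reading of an ambiguous sentence. Most repeats of the threshold, including those in section 8.2 and on the reporting form, only tell the nurse when to record a reason. The safeguards are also real: a tablet banner for empty fields, and a nurse's completeness check at baseline.

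Much of this stands. Cross-scale filling is an inference, not a stated instruction, and the repeats do not set the scoring rule. The discard half needs no inference, however: "the questionnaire will not be considered valid" is said of the questionnaire. The manual's content is not in the protocol, its citation number matches nothing in the unnumbered reference list, and a general deferral does not override an explicit sentence. The open imputation clause adds a second, unnamed method and resolves nothing. Nor was the matter simply left to the SAP: the protocol states a rule, and it states a subscale rule for the HADS.

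Two stronger readings are tempting. A reader might turn the expected 2% into 1 to 2% of questionnaires lacking both social items, that is 6 to 12 of 576. The documents do not support that step; independent omission gives about 0.2 of 576. A reader might also infer a biased treatment effect. That needs skipping to differ between control and post-intervention periods. The protocol expects missing values to be spread at random across the two groups, and nothing in it shows otherwise.

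**Conclusion.** The point holds as a badly fitted rule for scoring the primary endpoint, with a small expected effect. The completeness threshold and the validity rule are worded for the whole questionnaire, the primary analysis is by domain, and no text gives a per-scale rule for the QLQ-C30. Loss of complete primary domains follows from the literal text. Acceptance of a questionnaire with an empty primary domain follows too; filling that domain from other scales is permitted by the wording but not clearly prescribed.

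Under scattered 2% omission, fewer than one of 1,296 assessments lacks both social items, and the discard case practically never arises. The practical risk is therefore block non-response, or patients declaring that they do not wish to answer, which the tablet banner allows. The protocol gives no rate for either. The pattern of stopping after item 16 or starting at item 17 follows the page break of the attached form, and tablet screens may differ. The item counts rest on the assignment of items to domains by their wording.

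**What to change.** Amend section 8.9, and carry the same wording into the SAP:
- Apply the half rule within each QLQ-C30 scale. If at least half of that scale's items are answered, its missing items take the mean of the answered items of the same scale.
- If fewer than half are answered, set that scale alone to missing.
- Include a patient in the analysis of a domain whenever that domain can be scored at the required time points, whatever the state of the rest of the questionnaire.
- Delete the clause on an imputation method to be chosen as most appropriate.
- Keep the questionnaire-level threshold only as the trigger for recording reasons for non-completion, as in section 8.2 and the reporting form.

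This costs a few sentences and needs no new data, no change to the form and no change in sample size. It should be settled before database lock, so that no discretion remains over primary scoring.

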### 2. *Missing questionnaire*

If no response is given, or if the number of missing responses exceeds half of the items, the research nurse will report the reasons in the eCRF, i.e. patient participation withdrawal, refusal to complete the questionnaire without providing any reason, deterioration of health conditions precluding completion, lost to follow-up. During data analysis, as suggested by Fayers and Machin [Fayers 2000], reasons for failure to complete the questionnaire will be used as covariates in a logistic regression model, to investigate the association between compliance and indicated reasons.

## 9. MONITORING

Centralized trial monitoring will be carried out at the Research and Innovation Unit. During data collection, entered data will be systematically checked and a report will be prepared for each center, indicating expected questionnaires, questionnaires that were included, and those deemed not valid. All errors, incongruences, and omissions will be summarized in Data Query Forms, which will be sent to the investigators to elicit the necessary corrections. Investigators will be in charge of making the appropriate changes to the data of their center.

## 10. FEASIBILITY STUDY

Before the randomized trial begins, a pilot study will be performed at the cancer center of Cremona, on a consecutive sample of eligible patients who access the facility over two weeks (approximately 30 patients). This investigation aims to measure feasibility and acceptability of questionnaire

administration using a tablet. For this purpose, the following aspects will be recorded: the frequency of subjects declining participation in the survey and the corresponding reason (e.g. the use of a tablet), time taken by patients to complete the three instruments (HRQoL C30, HADS and NEQ), perceived difficulty and appreciation for the use of the tablet (expressed on a 5-point Likert scale [Abernethy 2009, Mark 2008])

## **11. Ethics and regulatory aspects**

The study will be conducted in compliance with the principles of the revision of the Helsinki Statement and the legislation on scientific research. The protocol and patient informed consent will be submitted to the Ethics Committees (ECs) of the Hospital of Cremona and of all participating centers according to current Italian legislation. Before the trial is started at each center, authorization from the hospital's legal representative will be requested.

### **11.1 Informed consent**

This study does not imply any type of experimental pharmacological treatment, or changes to diagnostic –therapeutic practice. Since the HQIS is implemented at each center regardless of patient informed consent signature, eligible patients will be asked to consent to the handling of their personal data. The informed consent form will be dated and signed by the patient and by the physician, authorized in accordance with regulations of the center's local EC. Information sheet and consent form for data handling will be used also for the feasibility study.

The informed consent form prepared by the coordinating center may be modified following specific requests of the local ECs. A copy of the signed informed consent shall be given to the patient and the original version retained by the center's investigator as part of the study documentation. It is the investigator's responsibility to obtain written informed consent to the use of health information. If a patient chooses not to continue with the study, it is the investigator's responsibility to ensure that no more health data of this person are collected. All gathered data will be used in the final analysis.

### **11.2 Confidentiality**

All data collected, processed and stored for the purposes of the project will remain confidential at all times in compliance with GCP guidelines and current privacy regulations. Data will be gathered anonymously and sent to the study group in charge of data analysis and management, using a data communication system based on the HTTPS protocol (<https://www.w3.org/2001/tag/doc/web-https>) to ensure secure connections. Patients can only be identified by the clinical staff operating at the center where they were recruited. Each patient will receive personal credentials which he/she will use to complete the questionnaires. The research nurse will be in charge of sending the information to the central database. Backup will be performed daily on the central database.

## 12. ORGANIZATION AND RESPONSIBILITIES

### 12.1 Coordinating center

The trial will be coordinated by the Oncology Unit of the hospital of Cremona which assigns part of the activities to the Research and Innovation Unit of the University-Hospital of Parma, as follows: center recruitment and organization of training courses (Cremona), project management (Cremona), eCRF creation for tablet and training (Parma), data management and statistical data processing (Parma). The center of Cremona will also be in charge of obtaining the necessary authorizations to Ethics Committees and maintain contacts with clinical centers in the study.

### 12.2 Scientific Committee

The Scientific Committee (SC), also comprising independent members, is in charge of overall trial oversight and performs strategic guiding through periodic meetings during which it is informed by the coordination team on ongoing work, on any critical issues that have emerged and possible actions to undertake. The SC is responsible to decide whether a process must be stopped or modified.

### 12.3 Principal Investigators of participating centers

For each center, a study principal investigator is identified, in charge of:

- Be a liaison between the EC and center administration to ensure timely authorization
- Ensure efficient communication with the coordinating center
- Ensure adherence to the scientific protocol
- Ensure necessary recruitment
- Ensure adequate data collection and act as guarantor for data integrity and quality
- Ensure collaboration to solve any issues that may arise during the process of database quality control.
- Rapidly report to the Project manager any problems arisen during trial conduction at the center

### 12.4 Original document storing

Investigators shall keep at their center the documentation of each enrolled patient: documentation supporting eligibility and the original informed consent form signed by the patient. Investigators shall also prepare a folder (Investigator's File, IF) containing: all study documentation approved by the EC, including amendments and minutes, CRF, signed agreements, curriculum vitae of the investigator /s co-investigator/s, registry of enrolled subjects, list of subject identification codes. All documentation shall be kept for at least seven years after the end of the study, as required by current norms.

### 12.5 Publication of results

AIOM is the study promoter. The Unit of Cremona, the coordinating center, holds property of the database. Data will be published under the responsibility of the SC. Authorship will be determined by the SC by unanimous consensus and in accordance with usual rules for authorship attribution accepted internationally by the most authoritative journals, which essentially require fulfilment of the following criteria:

- 1) Substantial contributions to the conception or design of the work; or the acquisition, analysis, or interpretation of data for the work; 2) drafting the work or revising it critically for important intellectual content ; 3) final approval of the version to be published .

Author contribution to study design, enrolment, data analysis and manuscript drafting will therefore be considered for the definition of author order. Any request from the investigators to perform additional analyses for publications or conference presentations shall be submitted to the SC for evaluation and authorization. The SC shall receive a copy of every presentation, manuscript or abstract before dissemination.

